### Assessments

Data on demographics (age, gender, date of birth, education, income, employment, marital status, weight, height, physical activity history, and personal characteristics) and potential psychological moderators (i.e. index of autonomous functioning) will be collected only at baseline.

The primary outcome of this study is running behavior, which will be measured at baseline, intervention's end and 6-month follow-up by self-report (frequency and minutes of running per week). At 12 months, participants will be asked by telephone whether they keep running (at least) at their initial level, or not.

Secondary outcomes will include putative mediators and outcomes. Basic psychologic need satisfaction will be assessed via the Psychological Need Satisfaction in Exercise Scale (Wilson, Rogers, Rodgers, & Wild, 2006); Basic psychological need frustration will be assessed trough the Basic Psychological Need Frustration in Exercise Scale (Chen et al., 2015); Motives and gains via Exercise Motives and Gains Inventory (Ingledew, Markland, & Strömmer, 2014); Behavioral regulations will be assessed via the Behavioral Regulation in Exercise Questionnaire – 3 (Cid et al., 2018); Self-determination trait will be assessed via the Index of Autonomy Functioning (Weinstein, Przybylski, & Ryan, 2012); Self-regulation skills will be measured trough the Action planning, Coping planning, and Action control scales (Sniehotta, Scholz, & Schwarzer, 2005a; Sniehotta, Schwarzer, Scholz, & Schuz, 2005b); Self-efficacy will be assessed via the Modified Bandura's Exercise Self-Efficacy Scale (Bandura, 1997); Automaticity will be measured trough the Self-Report Behavioural Automaticity Index (Gardner & Tang, 2014; Gardner, Abraham, Lally, & de Bruijn, 2012); and exercise identity via the Exercise Identity Scale (Anderson & Cychosz, 1994). Regarding psychological outcomes, flow will be measured through the Dispositional Flow Scale – 2 in Exercise (Jackson & Eklund, 2002); Vitality will be assessed through the Subjective Vitality Scale (Ryan & Frederick, 1997); and passion through the Passion Scale (Cid et al., 2019).

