### Analytical strategy

Statistical analysis will be performed using SPSS Statistics version 25.0 (SPSS Inc., an IBM Company, Chicago IL, USA). Descriptive statistics will be calculated (mean, standard deviation and range). Repeated measures with Bonferroni corrections for adjusted comparisons will be used to examine differences between each intervention group(PNMC or SRM) and controls (i.e. free recreational runners), at all assessment points, in the primary and secondary outcomes measured. Statistical significance will be set at *p* < 0.05.

Mediation analysis, will test the psychological mechanisms underlying changes in running behavior from baseline to post program, 6 and 12 months. Multilevel modeling will be used to determine the SRM intervention effect on these motivational variables, with intervention group (SRM vs. Control group) as the between-subject factor and change in self-regulation and competence for running at baseline, 6–8 weeks, 6months and 12 months, serving as dependent variables. If necessary, multiple imputation methods will be implemented to provide robust results for primary and main secondary outcomes.

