### Power calculations and sample size estimation

Two types of sample size calculations were made: (a) using the primary outcome – running minutes and (b) using secondary outcomes, in particular, changes on key psychosocial variables. Regarding our primary outcome, we have used vigorous physical activity for our calculations. A small effect size (Cohen's *d *= 0.23) is expected, a value previously registered in studies with intrinsic motivation interventions (Ntoumanis et al., 2020; Sheeran et al., 2020). Considering a power of 0.8 with two-tailed analysis, we estimated that each intervention group should have 37 (*p *= 0.05) or 55 participants (*p *= 0.01). Concerning our secondary outcomes, we are expecting effects sizes ranging from 0.23 to 0.73, based on previous reports (Ntoumanis et al., 2020; Sheeran et al., 2020). Thus, assuming an effect size of 0.50, 18 subjects/group will be required to detect significant differences at *p *= 0.05 and 28 for *p *= 0.01. Given that the primary outcome is expected to have a smaller effect size, and expecting a dropout rate of 15% at follow-up, we estimate that approximately 55 subjects/group are needed at baseline (for *p *= 0.05). Thus, recruiting 220 participants will ensure high statistical power for our primary analyses, extending its power to the secondary analyses.

Trial results will be published in peer-reviewed scientific journals and in several international and national scientific conferences. The website will be our central media to promote the dissemination of the results to the general public. Other media will be reached through university partners and website.

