#### Pilot participant characteristics

The CONSORT diagram for the pilot is shown in Figure 5. In total, 18 participants were enrolled and completed the baseline assessment. Of those, 3 dropped out during the intervention, allegedly due to time constraints and injuries; 15 participants finished the 6 week-intervention, 7 the post-program questionnaire, and 14 the overall study satisfaction questionnaire.

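### Running minutes are to be analysed by an unspecified repeated-measures method with imputation left to discretion, although the pilot makes substantial questionnaire loss plausible

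*Protocol article*

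**What the plan says.** All references are to the protocol article.

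- **Outcome (Assessments).** "The primary outcome of this study is running behavior, which will be measured at baseline, intervention's end and 6-month follow-up by self-report". The 12-month measure is a separate yes/no item: "At 12 months, participants will be asked by telephone whether they keep running (at least) at their initial level, or not". Under Data collection, running minutes and frequency at 6 weeks and 6 months sit in the same online battery as the psychological scales, estimated at about one hour.
- **Primary comparison (Analytical strategy).** "Repeated measures with Bonferroni corrections for adjusted comparisons will be used to examine differences between each intervention group" and controls. The text does not say whether this is a repeated-measures analysis of variance or a mixed model.
- **Motivational variables (same section).** "Multilevel modeling will be used to determine the SRM intervention effect on these motivational variables".
- **Missing data (same section).** "If necessary, multiple imputation methods will be implemented to provide robust results for primary and main secondary outcomes". No condition that would trigger imputation is given.
- **Planned loss (Power calculations and sample size estimation).** "expecting a dropout rate of 15% at follow-up, we estimate that approximately 55 subjects/group are needed at baseline". For the primary outcome, "A small effect size (Cohen's *d *= 0.23) is expected".
- **Pilot (Pilot participant characteristics).** Of 18 enrolled, 15 finished the six weeks, 14 completed the satisfaction questionnaire and 7 the post-program questionnaire.
- **Injury.** Eligibility criteria list an injury during the study as an exclusion. Data collection has eligibility re-checked by telephone before the 6- and 12-month assessments.

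**The concern.** Multilevel modelling is named for the motivational variables and a differently named method for the primary outcome. The natural inference is that the primary method is something else, most likely the general linear model repeated-measures procedure in SPSS. That procedure drops a participant who lacks any one of the repeated assessments. The only protection is then imputation, which the analysts may or may not invoke after seeing the data.

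Two things are at stake. The first is precision: partial responders, who supply usable information, may be discarded. The second is bias. The trial is about relapse, and people who stop running may be less inclined to return a long questionnaire on running. Of the pilot leavers the article says "3 dropped out during the intervention, allegedly due to time constraints and injuries", and either reason could also lead someone to stop running. If that link were stronger in one arm than another, the comparison among returners would be distorted. Neither a complete-case analysis nor standard imputation would show it.

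**Working it through.** **1. The plan's own allowance.** With 55 per group and 15% dropout, 55 × 0.85 = 46.75 remain per group, above the 37 per group that the plan states for p = 0.05. The plan's own step does not reproduce: 37 / 0.85 = 43.5, so 44, whereas 55 is its p = 0.01 figure before dropout. A two-sample comparison at d = 0.23, two-sided 0.05 and 80% power needs 297 per group, not 37. That is a separate matter, and nothing below relies on it.

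**2. What the pilot returned.** Non-return of the post-program battery was 11/18 = 61% (exact 95% CI 36% to 83%). Among those who finished the six weeks it was 8/15 = 53%. If the true rate were 15%, the probability of 11 or more missing out of 18 is about 0.00001.

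**3. Complete cases per group, starting from 55.**
- 15% lost in total: 46.75.
- 15% missing independently at each of two follow-ups (an assumption the article does not state): 55 × 0.85 × 0.85 = 39.7 complete, with 46.75 observed at each visit.
- Pilot return rate: 55 × 7/18 = 21.4.
- Complete cases fall below the plan's own 37 once loss exceeds 1 − 37/55 = 33%. The lower pilot limit of 36% is already past that.

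**4. Bias in a completer comparison.** Let *m* be the missing share in an arm and *g* the gap, in SD units, by which returners exceed non-returners in mean running minutes. The full-arm mean is the returner mean minus *m* × *g*, so completers overstate the arm by *m* × *g*. With subscript 1 for the intervention arm and 0 for its comparator:

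bias in the difference = *m*₁*g*₁ − *m*₀*g*₀

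The gaps and the unequal missing shares are assumed; the article gives none.

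| *m*₁ | *m*₀ | *g*₁ | *g*₀ | Bias (SD) |
|---|---|---|---|---|
| 0.15 | 0.15 | 0.5 | 0.5 | 0 |
| 0.61 | 0.61 | 0.5 | 0.5 | 0 |
| 0.15 | 0.15 | 0.5 | 0 | 0.075 |
| 0.61 | 0.61 | 0.5 | 0 | 0.305 |
| 0.20 | 0.10 | 0.5 | 0.5 | 0.05 |
| 0.61 | 0.40 | 0.5 | 0.5 | 0.105 |

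Across the pilot interval, a 0.5 SD gap in one arm only gives 0.36 × 0.5 = 0.18 to 0.83 × 0.5 = 0.415. To equal the expected effect of 0.23, that gap needs 0.23 / 0.5 = 46% missing. At the planned 15%, the gap in one arm would have to be 0.23 / 0.15 = 1.53 SD. If the gap lies in the comparator arm instead, the sign reverses.

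**5. What each method repairs.** A mixed model or standard multiple imputation keeps partial responders and is valid if data are missing at random given what was observed. Neither removes bias when non-return depends on unobserved relapse. Only an analysis that departs from that assumption shows how far the conclusion depends on it.

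**The case against.** The case on the other side has substance.

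- **The analysis plan is not shown.** The imputation model, its trigger and sensitivity analyses are commonly placed there, so their absence from an article is not counted here. What remains is what the article does state: a method named for the primary outcome that differs from the one named for the mechanism variables, and imputation made conditional.
- **The method is never named as listwise-deleting, and imputation is offered for the primary outcome.** Both are true. A reader might infer that the trial will be judged only on those who stayed. The document does not support that as a certainty, because it needs the unfavourable reading of the method and a decision not to impute.
- **Pilot loss may reflect burden rather than relapse.** This stands. Fourteen of 18 answered the satisfaction questionnaire, 83.3% found the questionnaire too long, and the Discussion tentatively cites length and the summer break and says the main trial should shorten it. The pilot had no control arm, and its participants averaged 6.3 years of running. Its return rate may not carry over, and it says nothing about differences between arms.
- **The 12-month item is a telephone question.** Online non-return therefore does not apply to it directly. It would also be a mistake to illustrate the primary outcome with relapse percentages, since that outcome is weekly minutes and frequency.
- **Planned dropout is most naturally cumulative.** On that reading about 47 complete cases remain, and the fall to 40 depends on an added assumption.

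None of this makes a discretionary rule adequate. The observed data cannot show whether loss is tied to relapse or differs by arm.

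**Conclusion.** The point holds in conditional form. The article leaves the primary analysis open to deletion of partial responders and makes imputation discretionary, while its own pilot lost 61% (36% to 83%) of the post-program questionnaires against 15% planned. Substantial loss is plausible but not established.

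The size of any bias is unknown. It is zero under equal missing shares and equal gaps, about 0.08 SD at 15% missing and about 0.31 SD at 61% if non-returners are 0.5 SD lower in one arm only. These last two figures rest on an assumed gap and on completer-only analysis. A reader might infer that the result would be biased in favour of the intervention. The document does not support a direction, nor a demonstrated link between non-return and relapse.

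The change is still worth making before outcome data are seen, because a better method is already planned for other variables and costs little.

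**What to change.** 1. In Analytical strategy, name a mixed model for running minutes at baseline, 6 weeks and 6 months, using every available observation in the allocated arm. State that it is valid under missing at random: it recovers partial responders but does not remove relapse-driven bias.
2. Replace the conditional imputation sentence with a fixed sensitivity analysis. Impute running minutes, shift the imputed values downward over a stated range, separately by arm and including shifts in one arm only, and report the shift at which the conclusion changes.
3. For the 12-month telephone item, add an analysis that counts non-responders in every arm as not maintaining.
4. Reconcile the injury exclusion and the later re-screening with analysis by allocated arm. As written, a participant injured after randomization could leave the comparison, and it is unclear how items 1 to 3 would treat that person.

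The cost is revised wording and somewhat more analysis, with the mixed model in the software already planned. No further data collection is needed. The drawback is that the sensitivity results may look less favourable than the main analysis.

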### Power calculations and sample size estimation

Two types of sample size calculations were made: (a) using the primary outcome – running minutes and (b) using secondary outcomes, in particular, changes on key psychosocial variables. Regarding our primary outcome, we have used vigorous physical activity for our calculations. A small effect size (Cohen's *d *= 0.23) is expected, a value previously registered in studies with intrinsic motivation interventions (Ntoumanis et al., 2020; Sheeran et al., 2020). Considering a power of 0.8 with two-tailed analysis, we estimated that each intervention group should have 37 (*p *= 0.05) or 55 participants (*p *= 0.01). Concerning our secondary outcomes, we are expecting effects sizes ranging from 0.23 to 0.73, based on previous reports (Ntoumanis et al., 2020; Sheeran et al., 2020). Thus, assuming an effect size of 0.50, 18 subjects/group will be required to detect significant differences at *p *= 0.05 and 28 for *p *= 0.01. Given that the primary outcome is expected to have a smaller effect size, and expecting a dropout rate of 15% at follow-up, we estimate that approximately 55 subjects/group are needed at baseline (for *p *= 0.05). Thus, recruiting 220 participants will ensure high statistical power for our primary analyses, extending its power to the secondary analyses.

Trial results will be published in peer-reviewed scientific journals and in several international and national scientific conferences. The website will be our central media to promote the dissemination of the results to the general public. Other media will be reached through university partners and website.

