#### Pilot study participants

Pilot participants were recruited among the running community through online advertisement. Study procedures were equivalent to those defined for the RCT, except that participants were not randomized, following the path of the study as if they were included in the intervention group. Participants were informed about the results of this pilot by individual reports.

The pilot feasibility study was a 6-week non-controlled trial without the follow-up. Considering an expected effect size of 0.23, 55 subjects per arm should be required in the main trial to detect significant differences at *p *= 0.05 (see sample size calculations for the main trial). Bearing in mind the rule of thumb for pilot sample size (Bell, Whitehead, & Julious, 2018), for an 80% powered main trial, with an expected medium effect size, the pilot should have between 10 and 15 subjects per arm.

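### The sample sizes of 37/55 (d = 0.23) and 18/28 (d = 0.50) per group cannot be reproduced from the stated inputs, and 220 participants do not give high power for the planned pairwise comparisons

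*Protocol article*

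**What the plan says.** The section on power calculations and sample size estimation describes two calculations, one for the primary outcome (running minutes, using vigorous activity as the basis) and one for changes in psychosocial secondary outcomes.

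- Primary outcome: expected Cohen's d of 0.23. "Considering a power of 0.8 with two-tailed analysis, we estimated that each intervention group should have 37" at p = 0.05, or 55 at p = 0.01.
- Secondary outcomes: "assuming an effect size of 0.50, 18 subjects/group will be required to detect significant differences" at p = 0.05, and 28 at p = 0.01.
- After allowing for 15% dropout: "we estimate that approximately 55 subjects/group are needed at baseline", given as the p = 0.05 figure.
- Conclusion: "Thus, recruiting 220 participants will ensure high statistical power for our primary analyses, extending its power to the secondary analyses".

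The section on pilot study participants repeats the result, again at p = 0.05: "Considering an expected effect size of 0.23, 55 subjects per arm should be required in the main trial".

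The analytical strategy plans repeated-measures analyses that compare each intervention group with the free-runner controls, with Bonferroni correction, at a significance level of 0.05. The number of comparisons in the Bonferroni family is not given. Neither section gives a correlation between measurements, a number of occasions or an ANOVA effect size as an input to the sample size.

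**The concern.** An effect of 0.23 SD is small, and 37 per group is far below what a two-group comparison normally needs to detect it. The dropout step does not lead from 37 to 55 either, and 55 appears both as the 0.01 figure before dropout and as the 0.05 figure after it.

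The trial's size rests on this paragraph. If its figures are wrong, a reader who accepts the power claim has no warning that a non-significant primary result is the likely outcome even when the assumed effect is real.

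**Working it through.** **Inputs.** From the sample-size section: d = 0.23 or 0.50, power 0.80, two-tailed, alpha 0.05 or 0.01, dropout 15%, 55 per group. The analytical strategy supplies the comparison: each intervention group against controls.

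**1. Attempt to reproduce the stated figures.** The normal approximation is n per group = 2 × (z₁₋α/₂ + z₀.₈₀)² / d². The squared sum is 7.849 at alpha 0.05 and 11.679 at alpha 0.01.

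| d | alpha | Calculation | Normal | Exact t, rounded up | Article |
|---|---|---|---|---|---|
| 0.23 | 0.05 | 2 × 7.849 / 0.0529 | 296.7 | 298 | 37 |
| 0.23 | 0.01 | 2 × 11.679 / 0.0529 | 441.5 | 444 | 55 |
| 0.50 | 0.05 | 2 × 7.849 / 0.25 | 62.8 | 64 | 18 |
| 0.50 | 0.01 | 2 × 11.679 / 0.25 | 93.4 | 96 | 28 |

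None of the four is reproduced. One-sided testing (234 and 380 per group at d = 0.23) does not reach 37 or 55 either.

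**2. Dropout.** 37 / 0.85 = 43.5, so 44 per group, not 55. In the other direction, 55 × 0.85 = 46.75, so 47 analysed per arm.

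**3. Power of the planned pairwise comparisons with 47 per arm** (exact noncentral t)
- d = 0.23, alpha 0.05: about 20%. By the normal approximation, 0.23 × √(47/2) = 1.115, and 1.115 − 1.960 = −0.845, which gives about 0.20.
- d = 0.23 with Bonferroni: about 13% if the family is assumed to be 2 comparisons, about 10% if 3.
- d = 0.50, alpha 0.05: about 67%.
- Detectable d at 80% power: 2.802 × √(2/47) = 0.578 by the normal approximation and 0.584 exactly, so about 0.58.

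With no dropout at all (55 per arm), power at d = 0.23 is about 22%.

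**4. Could baseline adjustment explain the figures?** Multiply n by (1 − ρ²), where ρ is an assumed baseline-to-follow-up correlation. The need falls from 297 to 223 (ρ = 0.5), 152 (0.7), 107 (0.8) or 57 (0.9). Reaching 37 takes ρ = √(1 − 37/297) ≈ 0.94. Power with 47 per arm becomes about 25% (ρ = 0.5), 34% (0.7) or 45% (0.8).

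**5. Could a group-by-time test explain them?** Setting f = d/2 (0.115 and 0.25), with assumed correlations:

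| Setting | d = 0.23, alpha 0.05 / 0.01 | d = 0.50, alpha 0.05 / 0.01 |
|---|---|---|
| 4 groups, 4 occasions, ρ = 0.5 | 37.75 / 51.75 | 8.75 / 11.75 |
| 2 groups, 3 occasions, ρ = 0.7 | 37.5 / 54 | 9 / 12.5 |
| Article | 37 / 55 | 18 / 28 |

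Both come near 37 and the second also near 55, but neither gives 18 or 28. Using d/2 as the interaction f also assumes more than d = 0.23: with two groups and two occasions, f = 0.115 is a between-group difference in change of 4 × 0.115 = 0.46 SD. The first setting is a global test on 9 degrees of freedom, not a comparison with controls, and it counts 12 months as an occasion although minutes are not collected then (Assessments).

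**6. For information: pooling over strata.** SRM against no SRM gives 2 × 47 = 94 per side. The detectable d is about 0.41, and power at d = 0.23 is about 35%. With baseline adjustment at an assumed r = 0.5, these become about 0.36 and 44%.

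**The case against.** The strongest defence is that the analysis is a repeated-measures one, that a journal article condenses the full protocol, and that the test and correlation behind 37 may be recorded there. Step 5 shows that such a test can come close to 37 and 55. This much stands: the shortfall of about eightfold (298/37 and 444/55) is specific to a simple two-group comparison and should not be quoted without that condition. The defence does not rescue the figures. It needs an unstated correlation, builds in an effect larger than the stated d, and leaves 18 and 28 unexplained.

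Two further readings are tempting but unsupported.

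- That 55 is the 0.01 figure carried over under the wrong label. The text does not show this. It says approximately 55, and a deliberate choice of the larger number is possible and conservative relative to 37. What can be said is that 55 is unexplained at 0.05.
- That the two pairs contradict each other because n should scale with 1/d². That holds only if one method served both. The article says two calculations were made, for different outcomes. Each pair fails the two-group check on its own, which is enough.

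**Conclusion.** The point holds. The four sample sizes do not follow from the inputs given, and the claim of high power is unsupported for the primary outcome and for secondary outcomes at d = 0.50. With 47 analysed per arm, the planned comparisons with controls have about 20% power at d = 0.23 and about 67% at d = 0.50, with a detectable d of about 0.58, roughly 2.5 times the expected effect (0.58/0.23).

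These figures assume an unadjusted two-sided two-group comparison at 0.05 and the article's own 15% dropout. The 13% and 10% after Bonferroni rest on an assumed family of 2 or 3. Baseline adjustment would raise power, but at assumed correlations up to 0.8 it stays below one half at d = 0.23.

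A reader might infer that the trial has to be enlarged, or that the pooled SRM contrast must become primary. Neither follows. The error lies in the stated justification; changing the sample size, the target effect or the primary contrast is a separate decision.

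**What to change.** In the section on power calculations and sample size estimation:

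1. Withdraw 37, 55, 18 and 28 and the sentence claiming high power for 220 participants.
2. Keep 220, and state what it gives for the planned pairwise comparisons after 15% loss (47 per arm): 80% power for d of about 0.58, about 20% for d = 0.23 and about 67% for d = 0.50, before Bonferroni. Name the Bonferroni family and give the corrected power.
3. If credit is taken for baseline adjustment or repeated measurements, show it under a stated, assumed correlation.

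In the section on pilot study participants, correct the repeated statement that 55 per arm suffices for an effect of 0.23 at p = 0.05.

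As additional information, the article could report the pooled SRM versus no-SRM contrast stratified by PNMC/FRR (94 vs 94), using the figures in step 6. It fits the stratified 1:1 randomisation and the hypothesis in the Discussion. Making it the primary contrast would require amending the analytical strategy.

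The correction itself costs wording only and no extra participants. The stated power becomes much less favourable.

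### The 15% dropout allowance does not turn 37 per group into 55: on the article's own inputs it gives 44 (176 in total, not 220)

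*Protocol article*

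**What the plan says.** All of the following is in the protocol article.

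- **Power calculations and sample size estimation, effect and power.** "A small effect size (Cohen's *d *= 0.23) is expected" for the primary outcome, with the power stated as "Considering a power of 0.8 with two-tailed analysis".
- **Same section, base numbers.** Before any mention of dropout: "each intervention group should have 37 (*p *= 0.05) or 55 participants (*p *= 0.01").
- **Same section, dropout step.** "expecting a dropout rate of 15% at follow-up, we estimate that approximately 55 subjects/group are needed at baseline". A bracket right after this labels the number p = 0.05, and the next sentence gives a recruitment total of 220.
- **Study design.** There are four groups, so 220 is 4 x 55.
- **Analytical strategy.** "Statistical significance will be set at *p* < 0.05".
- **Pilot study participants.** For an effect size of 0.23, "55 subjects per arm should be required in the main trial to detect significant differences at" p = 0.05. The sentence refers back to the main-trial calculation and does not mention dropout.

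**The concern.** One number, 55, does two jobs in a single paragraph. It is the pre-dropout size at p = 0.01 and also the post-dropout size at p = 0.05. A 15% allowance cannot carry 37 to 55, so the recruitment target does not follow from the inputs offered for it.

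As written, a reader cannot tell what loss the target tolerates: the stated 15%, or the one third that the numbers imply. That matters here. Under Pilot participant characteristics, 3 of 18 dropped out during the intervention and only 7 of 18 completed the post-program questionnaire. The primary outcome is self-reported, so an unreturned questionnaire is a missing primary outcome. The pilot differed from the planned trial (long-time runners, and a questionnaire that is to be shortened), so its rates do not carry over directly. They do show that the allowance is not a formality.

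**Working it through.** **Inputs, all from the article.** Base number 37 per group at 0.05 and 55 at 0.01; dropout 15%; four groups; power 80%, two-sided; d = 0.23; analysis alpha 0.05.

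**1. The printed total.** 4 x 55 = 220. This reproduces, so the total depends entirely on the 55.

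**2. The dropout step at the stated alpha.** Baseline number = completers/(1 - dropout).
- 37/0.85 = 43.5, so 44 per group and 4 x 44 = 176 in total.
- The cruder 37 x 1.15 = 42.6 gives 43, so a different inflation convention does not explain 55.
- The gap is 55 - 44 = 11 per group, or 44 people in total.

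**3. The loss that 55 implies.** 1 - 37/55 = 0.327, about 33%, against the stated 15%.

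**4. What 55 enrolled leaves.** 55 x 0.85 = 46.75, about 47 completers per group: more than the 37 said to be needed.

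**5. Whether 37 can serve as the base.** For a plain two-group comparison of means, n per group = 2(z_alpha/2 + z_beta)^2/d^2.
- d = 0.23, alpha 0.05: 2 x (1.960 + 0.842)^2/0.23^2 = 297 per group, against the printed 37.
- 297/0.85 = 349.4, so 350 per group after 15% dropout.
- Power with 47 per group: Phi(0.23 x sqrt(47/2) - 1.960) = Phi(-0.845), about 20%.
- Effect detectable with 80% power and 47 per group: (1.960 + 0.842) x sqrt(2/47) = 0.58.

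**6. Where 37 and 55 might come from.** The two agree with each other: (1.960 + 0.842)^2/0.46^2 = 37.1 and (2.576 + 0.842)^2/0.46^2 = 55.2. That is a one-sample formula with twice the stated effect. Some repeated-measures models also come close, but only with correlations that the article does not state. For example, with d = 0.23 read as f = 0.115, a group-by-time interaction with 3 groups, 2 measurements and an assumed correlation of 0.7 gives 38 and 55. The same model gives 9 and 13 at an effect size of 0.50, where the article prints 18 and 28. No model tried gave all four printed figures.

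**The case against.** The strongest defence is that the slip does no harm at the alpha the plan uses. The article needs 37 completers, enrols 55 and keeps about 47. On its own scale, where 37 completers correspond to 80% power, 46.75 give Phi(0.4606 x sqrt(46.75) - 1.960), about 88%. The target is also described as approximate. The direction of the error stands: relative to 37 it is conservative. Two things do not stand. A gap of 11 on 44 is 25%, which is more than rounding. And the 88% holds only if 37 is right for d = 0.23.

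Three stronger readings are tempting, and the documents do not support them.

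- **That the alpha is unclear, or that the trial is short at p = 0.01.** A reader might inflate 55 to 55/0.85 = 64.7, so 65 per group and 260 in total, and call the target 40 short. But the analysis section, the label on the final 55 and the pilot section all say 0.05. Nothing says the target serves 0.01.
- **That 55 was carried over from the p = 0.01 result.** The numbers are identical, which makes this plausible, but the article does not say so.
- **That 176 would be enough.** This accepts 37 as valid, which step 5 of the working does not support.

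Nor is the pilot section a second, independent error. It repeats the final figure and refers back to its source. Its own fault is that it does not say whether 55 is before or after dropout.

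**Conclusion.** The dropout step is wrong as written, and nothing else in the article repairs it. On the stated inputs, 37 per group with 15% loss becomes 44 (176 in total), not 55 (220); the printed figure implies about 33% loss. This part rests only on the article's own numbers.

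Taken alone, the inconsistency is modest: at alpha 0.05 it errs towards more participants than the article's base requires. It should still be corrected, because the recruitment target rests on it and restating it is cheap. The correction cannot stop at the inflation, since the base number is the larger problem.

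The figures of 297 per group and about 20% power assume a plain two-sided comparison of two groups, with no gain from baseline adjustment or repeated measures. If the intervention were compared with no intervention across both runner types, about 93.5 completers per side (2 x 46.75) would give about 35% power at d = 0.23, still far below 80%. A repeated-measures calculation could lower the requirement, but only with a correlation that the article does not give.

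**What to change.** 1. Correct the base completer number first. State the test, the effect-size metric and any assumed correlation, so that the number can be reproduced from d = 0.23 at alpha 0.05 and 80% power.
2. Restate the dropout step at alpha 0.05 as completers/(1 - dropout), and show the baseline number per group and the total.
3. If 220 is kept as the feasible total, say that 15% loss leaves about 47 per group, and print the power or detectable effect for 47 completers at 0.05. In a plain two-group comparison these are about 20% power for d = 0.23, or a detectable effect of about 0.58 with 80% power.
4. In the pilot section, say whether the per-arm figure is before or after dropout, and match it to the corrected calculation.

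If 220 is kept, the cost is one rewritten paragraph and one sentence, with no extra participants, but the stated power will change. If the aim remains 80% power for d = 0.23, the cost is recruitment: in the plain comparison about 350 per group, or 4 x 350 = 1,400 in total, unless a justified repeated-measures or covariate-adjusted calculation supports fewer.
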